### Data management and confidentiality

The data collected from the project will not be part of the subject’s clinical files. We will de-identify personal information and use codes instead. The computer files will be encrypted and password protected while data files, disks, and reports will be physically secured in a locked area with only authorized personnel having access to them. A master sheet with subject’s name and contact information will have to be maintained separately to enable initial review of their clinical information and contact throughout the study. De-identified data may be stored indefinitely. Records with identifiable data will be destroyed at the end of the study. Only authorized personnel listed on this IRB will have access to the data.

### Study endpoints

#### Primary outcomes

A simulated conversation (i.e., conversation with a speech-language pathologist) of the trained script will be recorded three times at baseline, immediately post-treatment, and at the 4- week and 8-week follow-up visits. The primary outcome measure is change in accuracy and rate of production on the trained script during a simulated conversation from pre- to immediately post-treatment.

#### Secondary outcomes

Secondary outcomes will be change from baseline to 4- and 8-week follow-up visits on the trained conversational script. We will also measure performance on an untrained script which will be matched for length and complexity using the Flesch-Kincaid readability index [40]. The untrained script will be used to assess generalization from pre- to post-treatment. Secondary outcomes will also include the change in WAB-R AQ from baseline to post-treatment.

### Statistical analysis

The primary outcome will be the change in performance (accuracy) from baseline to post-treatment on the trained script during a simulated conversation. Secondary outcomes will be (1) change in performance from baseline to 4 and 8 weeks post-treatment on the trained script during a simulated conversation, to assess maintenance, and (2) change in performance from baseline to post-treatment and baseline to 4 and 8 weeks post-treatment on the untrained script to assess generalization. Descriptive statistics (mean, SD, and 95% confidence intervals) will be used to summarize the data by groups. In addition, these outcomes will be analyzed using a two-sample *t*-test comparing changes from baseline to post-treatment between two treatment arms. The selected treatment arm will be compared to the sham tDCS arm. Paired *t*-tests will be used to determine whether changes in outcome persist at 4 and 8 weeks post-treatment persist (i.e., are they equal to 0). A more comprehensive analysis will be done using a mixed effects model which is robust to missing data to analyze changes over time.

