### Sample size and power

The study will enroll a total of 48 subjects (12 in each group). Power calculations were based on our previous work with similar participants, and planned two-tailed analyses (*α* = .05) for the primary outcome measure, the simulated conversation on the trained script.

In preliminary work without tDCS, we observed improvement in trained script accuracy at the end of language treatment relative to baseline was 10.4% (SD = 8.2%). Assuming similar variability in the proposed study, *n* = 12 subjects per group will allow us to estimate changes in accuracy with precision (half-width of a 95% confidence interval) of ±5.2% in each group. In addition, a sample size of *n* = 12 subjects per group will provide 80% power with two-sided *α* = 0.5 for a two-sample *t*-test to detect a 9.9% difference in accuracy improvement between treatment arms and the sham treatment (e.g., improvement in accuracy of 10.4% and 20.3% in the two arms, respectively).

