### Randomization

Participants will be randomized to each of the four treatment arms, i.e., four combination treatment sequences (tDCS prior to SLT, tDCS concurrent with SLT, tDCS following SLT, or sham tDCS (SLT only)). Randomization will be stratified by the baseline WAB-R AQ score (<60 vs. ≥60), and randomization will be conducted using the permuted block method. Randomization will be set by a statistician.

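### The planned between-arm t-test leaves out the WAB-R AQ stratum and fixes the baseline coefficient at 1; an adjusted model over all four arms would cost almost nothing and gain power if either covariate is prognostic

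*Protocol article*

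**What the plan says.** In the Protocol article, the Randomization section states: "Randomization will be stratified by the baseline WAB-R AQ score (<60 vs. ≥60", using permuted blocks.

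The Statistical analysis section defines the primary outcome: "The primary outcome will be the change in performance (accuracy) from baseline to post-treatment on the trained script during a simulated conversation". For the comparison between arms it says "these outcomes will be analyzed using a two-sample *t*-test comparing changes from baseline to post-treatment between two treatment arms", and then "The selected treatment arm will be compared to the sham tDCS arm". No covariate is named, and WAB-R AQ does not return as a stratum.

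The same section adds a further model: "A more comprehensive analysis will be done using a mixed effects model which is robust to missing data to analyze changes over time". Its terms are not listed, and its standing relative to the t-test is not stated.

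The Sample size and power section uses the same unadjusted test. It gives the size, "The study will enroll a total of 48 subjects (12 in each group", and the pilot variability, "improvement in trained script accuracy at the end of language treatment relative to baseline was 10.4% (SD = 8.2" percent).

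**The concern.** Stratifying by aphasia severity implies that severity is expected to predict the outcome. The design then balances the arms on it, so severity contributes little to the true variability of the difference between arms. An unadjusted t-test still counts the between-stratum variation in its error term. If the factor is prognostic, the standard error is too large, the interval too wide, and the nominal 5% test rejects less than 5% of the time under the null.

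Two smaller points go the same way. A change score subtracts baseline with a coefficient fixed at 1 instead of estimating it. And each test estimates its error variance from 24 participants although 48 are randomized.

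What is at stake is efficiency, not bias. It matters because there are only 12 per arm, the stated power is 80% with no margin described, and the Discussion intends the effect sizes to guide later trials.

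**Working it through.** **Inputs.** From Sample size and power: n = 12 per arm, SD of change 8.2, difference 9.9 points, two-sided α = 0.05. (That section also prints α as 0.5, which would give about 99% power; only 0.05 reproduces the plan.) Assumed, because the article does not give them: R², the share of change-score variance explained by the covariates, and r, the baseline-to-post correlation.

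**1. The plan's own figures.**
- Half-width: t(0.975, 11) × 8.2/√12 = 5.21 (stated 5.2).
- Standard error of a difference: 8.2 × √(2/12) = 3.348. Noncentrality: 9.9/3.348 = 2.957. With 22 df, power is 80.7% (stated 80%), and the difference detectable with 80% power is 9.81.

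The plan reproduces.

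**2. Omitting the stratum, two arms.** Simulated trials with 6 participants per stratum per arm (an assumed even split) and total SD held at 8.2. The t-test has 22 df and the stratum-adjusted test 21 df.

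| Variance explained by stratum | Type I error, t-test | Power, t-test | Power, adjusted |
|---|---|---|---|
| 0% | 5.0% | 81% | 81% |
| 10% | 3.9% | 82% | 84% |
| 20% | 2.8% | 83% | 88% |
| 30% | 1.9% | 84% | 92% |

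**3. One model over four arms, baseline accuracy and stratum as covariates.** Error df = 48 − 4 − 2 = 42. Standard error = 8.2 × √(1 − R²) × √(2/12) × √(1 + 2/41), where the last factor (1.024) allows for chance covariate imbalance.
- R² = 0: SE 3.428, noncentrality 2.888, power 80.5%.
- R² = 0.10: SE 3.252, noncentrality 3.044, power 84.5%.
- R² = 0.20: SE 3.066, noncentrality 3.229, power 88.4%.

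The t-test has 80.7%.

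**4. In terms of r.** With equal SDs before and after, replacing a change score by adjustment for baseline multiplies the variance by (1 + r)/2, so R² = (1 − r)/2.
- r = 0.5: SD 8.2 × √0.75 = 7.10, detectable difference about 8.5.
- r = 0.8: SD 8.2 × √0.90 = 7.78, detectable difference about 9.3.

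The t-test has 9.8. Part of this gain is not due to covariates: pooling variance over four arms with no covariate (44 df) already moves 9.81 to 9.59.

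**5. The same two covariates in a two-arm model.** With 20 df and imbalance factor √(1 + 2/19), power is 76.3% at R² = 0, 78.4% at 0.05, 80.5% at 0.10 and 84.9% at 0.20. Break-even with the t-test is near R² = 0.10, or r near 0.8 if baseline alone does the explaining.

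**6. Missing post-treatment values (dropout assumed).** The t-test has 76.8% power with 11 per arm, 72.4% with 10 and 67.2% with 9.

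**The case against.** The strongest reply is that nothing here is wrong. The sample size and the analysis rest on the same test, the stated power reproduces, and in every stratum scenario above the t-test keeps at least 80% power with type I error below 5%. The trial is labelled exploratory. Neither R² nor r is known, so the loss is conditional, and with weak covariates a two-arm adjusted model does worse than the t-test. All of this stands, and it limits the point to efficiency.

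It does not remove the point. The break-even near R² = 0.10 belongs to the two-arm model. Over four arms the cost at R² = 0 is about 0.2 percentage points of power. Nor is this a detail merely left to an analysis plan: the article fixes the unadjusted test and powers the trial on it.

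A reader might go further in three ways that the text does not support.
- That the primary test is restricted to completers. The article states no analysis population, imputation rule or dropout rate. A change score does need a post-treatment value, so dropping such participants is a fair inference if nothing is imputed, but no more. The 72% power assumes two dropouts per arm.
- That baseline is ignored. A change score adjusts for it with coefficient 1, which may be too much but is not nothing.
- That the mixed model is only secondary, or also omits the stratum. The article gives it neither a rank nor a list of terms.

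**Conclusion.** The point holds as one of efficiency. The planned test is valid and meets its stated 80% power with complete data. It omits the factor used to stratify, and it is conservative to the extent that this factor predicts change: type I error of about 3.9 to 1.9%, and a forgone 3 to 8 percentage points of power, if the stratum explains 10 to 30% of the variance.

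The case for the four-arm adjusted model does not depend on knowing R². Its worst case is close to parity with the t-test, and it gains about 4 points of power at R² = 0.10 and about 8 at 0.20. These figures assume SD 8.2 and similar variance in all four arms; those in r also assume equal SDs before and after treatment. It would be too strong to say that precision is certainly lost, because the prognostic strength of WAB-R AQ and of baseline accuracy for script learning is not given.

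**What to change.** Make the between-arm analysis of trained-script accuracy one linear model over all four arms: post-treatment accuracy on arm, baseline accuracy and WAB-R AQ stratum, with the active-versus-sham contrasts taken from it. Alternatively, give the planned mixed model these terms and name it as the main analysis; it would also use the available follow-up recordings when a post-treatment value is missing. Keep the two-sample t-test as supportive, and state which analysis carries the conclusion.

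The cost is a change of wording. WAB-R AQ and baseline script accuracy are already collected. The model spends two covariate degrees of freedom and assumes similar variance across arms, which can be checked by fitting arm-specific variances. Do not confine the adjusted model to the two arms being compared, since that version loses power if R² is below about 0.10.

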### Safety

The most often reported effects of tDCS are tingling and itching sensations under the electrodes, headaches, and tiredness [43]. These tDCS-induced sensations of tingling and itching can be associated with salinity of the solution used for electrode sponges [43]. Our electrode sponges will be soaked in a solution with appropriate NaCI solution concentration of 15 and 140mM [44]. We will inject saline into the electrode sponges periodically to make sure they are not dry. This will ensure that tDCS-induced discomforts due to dry electrode sponges are minimized [45]. In addition, self-reported tDCS-induced sensations will be obtained using aphasia-friendly questionnaires. The same questionnaires will be administered at the follow-up sessions. If discomfort is reported, we will assess whether the discomfort is common to tDCS (e.g., itching and tingling) and then make sure if the appropriate amount of saline is applied to the electrodes. We will also make a determination of the severity of tDCS-induced discomfort when it is brought to our attention. If we determine that these unanticipated effects are not tolerable for the participant, we will terminate the experiment.

## Discussion

This protocol describes a randomized clinical trial to investigate the timing of tDCS in combination with SLT for individuals with aphasia. This study is motivated by evidence for tDCS as a potential adjuvant to SLT [15, 16, 18]. Existing studies of tDCS in combination with SLT apply tDCS concurrently with SLT. It is presumed that performance improvements following online vs. offline tDCS are driven by different processes [26–29]. The objective of the current study is to investigate the role of timing parameters of tDCS relative to SLT. To our knowledge, our study is the first to evaluate the timing of tDCS relative to SLT for aphasia treatment.

Identifying the optimum timing to combine tDCS with SLT can guide treatment approaches to facilitate better outcomes for people with aphasia. Furthermore, the protocol described here uses fMRI-guided neuronavigation to identify the optimal site to apply tDCS electrodes. Locating the stimulation site in this way allows the specific lesion characteristics of each participant to be taken into account. A potential contribution of this approach is that it may help address issues of variability in other studies, where lesion site is variable but placement of tDCS electrodes is the same across participants [6].

The SLT used in this study uses a simulated real-world conversation. As such, the study may extend knowledge of tDCS in aphasia therapy beyond naming or word-level practice into the area of connected discourse. Lastly, the effect sizes derived from this study related to the particular treatment arm may guide other tDCS trials that investigate the impact of tDCS on functional communication in individuals with aphasia.

## Dissemination

Results from the study will be published in peer-reviewed journals and academic conferences.

## Trial status

The protocol version is 10.0 (2021). Recruitment began in 2018 and is expected to be completed by 2023.

## Data Availability

Data is available upon request at the end of the trial from the corresponding author.

## Abbreviations

PWA: Persons with aphasia
tDCS: Transcranial direct current stimulation
SLT: Speech-language therapy
WAB-R-AQ: Western Aphasia Battery-Revised-Aphasia Quotient
AG: Angular gyrus
pSTG: Left posterior superior temporal gyrus
IFG: Inferior frontal gyrus
LTP: Long-term potentiation
BCM: Bienenstock-Cooper-Munro
